## Abstract

**Background:**

The course and outcomes of hip fracture patients are often complicated by the presence of dementia and delirium, referred to as cognitive impairment (CI), which limits access to in-patient rehabilitation. In response to this concern, members of our team developed and piloted an in-patient rehabilitation model of care (Patient-Centred Rehabilitation Model; PCRM) targeting patients with hip fracture and CI (PCRM-CI). We are now conducting a 3-year study comparing an inpatient rehabilitation model of care for community dwelling individuals with hip fracture and CI (PCRM-CI) to usual care to determine whether it results in improved mobility at the time of discharge from inpatient rehabilitation.

**Methods/Design:**

A non-equivalent pre-post design is being used to evaluate the PCRM-CI compared to usual care. All community dwelling (private home or retirement home) patients following a hip fracture are eligible to participate. Recruitment of both cohorts is taking place at two facilities. Target accrual is 70 hip fracture patients in the PCRM-CI cohort and 70 patients in the usual care cohort. We are also recruiting 70 health care providers (HCPs), who are being trained to implement the PCRM-CI, and their unit managers. Patient data are collected at baseline, discharge, and 6 months post-discharge from an inpatient rehabilitation program. Evaluations include mobility, physical function, and living arrangement. Additional outcome variables are being collected from medical records and from the patients *via* their proxies. Data on the prevalence and severity of dementia and delirium are being collected. Staff data are collected at baseline and one year after implementation of the model to determine change in staff knowledge and attitudes toward patients with hip fracture and CI. Bi-monthly semi-structured interviews with unit managers have been conducted to examine factors and barriers influencing the model implementation. Data collection began in 2009 and is expected to be completed in 2012. The control cohort of 70 patients has been recruited, and 45 patients have been accrued to the intervention group to date.

**Discussion:**

Evaluation of this model of care is timely given the increasing proportion of persons with cognitive impairment and hip fractures.

**Trial registration:**

The study is registered at http://clinicaltrials.gov, Identifier NCT01566136.

## Background

A hip fracture is often a catastrophic event that results in significant impairment in mobility and function, and excessive institutionalization [1]. An estimated 25% to 75% of patients who are independent before their fracture can neither walk independently nor achieve their previous level of independent living within 1 year following the fracture [2]. Projections suggest that by 2041 the incidence of hip fractures in Canada will increase nearly four-fold [3], with an annual increase in economic burden of $2.4 billion per year [4], which is similar to other countries [5].

The course of hip fracture patients is often complicated by the presence of dementia and/or delirium. Dementia refers to a global loss of cognitive and intellectual functioning that gradually interferes with social and occupational performance [6]. Delirium is characterized by an acute decline in attention and cognition [7] and is linked to increased post-operative morbidity post-hip fracture [8]. Delirium may take weeks to months to diminish [9]. Both conditions are characterized by the presence of cognitive impairment (CI) across a spectrum of severity [8]. Two-thirds of cases of delirium occur in patients with dementia [10,11]. Studies have shown that 31 to 65% of older orthopedic patients have dementia and/or delirium [12]. As a result of the demographic shift to an aging population, the prevalence of dementia and the incidence of delirium in hip fracture patients are expected to progressively increase over the next 25 years [13]. In hip fracture patients, CI and low pre-fracture functional status are the most important predictors of poor prognosis regarding walking ability and return to independent living. [14].

Despite emerging evidence that patients with dementia and delirium can improve their mobility and function in rehabilitation [15,16], current health care services for people with a hip fracture and CI are fragmented and limited such that few patients are able to access rehabilitation services [4,17,18]. The lack of rehabilitation for these patients has negative consequences for the patients and the health care system: specifically, 1) hip fracture patients with CI have worse long-term mobility and functional outcomes compared to those without CI; and 2) many patients with CI have extended stays in acute care, some for several weeks, instead of being cared for in a less costly inpatient rehabilitation setting [19]. For those hip fracture patients with CI who are transferred to inpatient rehabilitation settings, the professional health care providers (HCPs) lack the necessary skills and knowledge about cognitive and behavioural strategies to care for them [20,21].

Despite research findings on rehabilitation, dementia, and delirium care, there are no rehabilitation models of care that combine these elements into a comprehensive model. To address this limitation we developed a model of care for all patients with hip fractures, with specific components of the model targeted for those patients with CI, referred to as Patient-Centred Rehabilitation Model (PCRM-CI). Our model is the first to include the following 5 components: rehabilitation management; dementia management; delirium prevention and management; staff education and support; and family/significant other support and education. Rationale for the separate components of the model is derived from the literature (Table 1).

**Table 1 T1:** Components of the Patient-Centred Rehabilitation Model Targeted for Patients with CI (PCRM-CI)

**Components**	**Provider (s)**	**Effects**
1. Rehabilitation Management	Nurse, Physician, PT, OT, SW, pharmacist	**↑** function (Hurito *et al.*, 2000)
- assessments of function and cognition		**↑** mobility (Adunsky *et al.*, 1999)
- patient goal setting		**↑** return to previous living
- interdisciplinary rehabilitation treatments		arrangement (Naglie et al., 2002)
- weekly meetings to discuss progress of patient		
- discharge planning from week one		
2. Dementia Management	Nurse, Physician, PT, OT	**↓** agitation (Kovach *et al.*, 2006)
- assessment (MMSE)		**↑** function (Kovach *et al.*, 2006)
- relate well		
- environmental manipulation		
- abilities focus		
- personhood		
3. Delirium Management	Nurse, Physician, PT, OT	**↓** complications (Fick *et al.*, 2007)
- assessment (CAM)		**↓** LOS (Millisen *et al.*, 2004)
- prevention		
- treatment		
4. Staff education and support	APN	
- 1 day workshop on dementia, delirium, depression, care approaches, strategies to minimize behavioural and cognitive symptoms.		**↑** attitude towards patients with dementia (Zimmerman *et al.*, 2006; McGilton *et al.*, 2007).
- 8 in-services on the following topics: sleep, falls prevention, team building, pain management, incontinence, bowel management, roles and responsibilities of rehabilitation team and team building.		**↑** knowledge and skill of care of elderly clients (Moniz-Cook *et al.*, 1998; Cohen-Mansfield *et al.*, 1997)
- Advanced practice nurse mentoring at the bedside		**↑** support and improvement in work environment and **↑** satisfaction caring for clients with dementia (Wells *et al.*, 2001)
5. Family/significant other education and support	Nurse, SW	**↓** nursing home placement (Mittleman *et al.*, 1996)

Note: *OT* occupational therapist; *PT* physiotherapist, *APN* Advanced practice nurse, *SW* social worker.

Care of persons with dementia and delirium was guided by the 4 principles underlying the REAP (Relate well, Environmental manipulation, Abilities focused and Personhood) model of care conceptualized by the Principal Investigator (PI) [22]. First, staff’s ability to relate well is an essential component of HCP-patient interactions [23,24]. Depending on the patients’ level of CI, they may have difficulty understanding words or following directions [25]. Staff are taught techniques to relate effectively to their patients. Second, person-environment theory [26] argues for the need for synergy between person and environment. The environment must be modified and changed to accommodate the person’s changing needs and preferences. HCPs are taught to control the daily activity schedule of the patient in order to maintain a balance between high and low arousal states [27]. Third, abilities focused care [28] involves staff focusing on patients’ retained abilities. The ability of persons with dementia to perform Activities of Daily Living (ADLs) is influenced by their performance of purposeful movements, understanding of spatial orientation, and the ability to initiate activities. HCPs are taught to follow the steps of asking, cueing and demonstrating, before doing the activity for the patient. Fourth, Personhood [29] refers to knowing a person, becoming familiar with the individual, gaining knowledge of a person’s life, and identifying “what makes them tick” [30]. This process may involve partnering with families to gain needed knowledge. An understanding of the individual assists HCPs to become aware of the patient’s unmet needs, such as pain, often manifesting as behavioural agitation [31].

The model was piloted on one musculoskeletal rehabilitation (MSK) unit at Toronto Rehabilitation Institute (Toronto Rehab) [32]. Results suggest that HCPs can learn to successfully rehabilitate hip fracture patients with and without CI utilizing this model [32]. Subsequently, the researchers decided to develop a demonstration project to address the following aims: 1) to evaluate the short and long-term patient outcomes associated with the PCRM-CI model of care as compared to usual care; 2) to determine if the PCRM-CI model can be replicated and sustained in a variety of community-based facilities that have different combinations of staff/patient ratios, staff skills, *etc.*; and 3) to establish, from a health human resource perspective, the influence on rehabilitation staff of caring for clients with CI. The overall purpose of this study is to establish a best practice model that will allow hip fracture patients with CI to regain their mobility and function. The findings of this research will have a major impact on the organization, management and delivery of services for the large and rising number of hip fracture patients with CI. The conceptual model for our study is depicted in Figure 1.

**Figure 1 F1:**
[figure not shown]
Patient-centred rehabilitation model of care targeting patients with CI (PCRM-CI).

## Specific objectives

### Primary objective

To determine whether the PCRM-CI model, an inpatient rehabilitation model of care targeting community dwelling individuals with hip fracture and CI (dementia and/or delirium), results in improved mobility at the time of discharge from inpatient rehabilitation.

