### Secondary objectives

1) To determine whether the PCRM-CI model for persons with hip fracture and CI results in: i) improved mobility at 6 months post-discharge from inpatient rehabilitation; ii) greater improvement in physical functioning at the time of discharge from inpatient rehabilitation and at 6 months post-discharge; iii) a higher proportion of patients returning to their previous living situation in the community at discharge and at 6 months post-discharge.

2) To determine whether the PCMR-CI model results in similar improvements in mobility at discharge from inpatient rehabilitation and 6 months post-discharge for patients with and without CI.

3) To evaluate whether the PCMR-CI model improves HCPs’ attitudes, knowledge, satisfaction, and stress, in caring for patients with CI.

4) To examine the processes by which the PCRM-CI model is implemented by describing: i) the evidence based components of the model that facilities adopt (*i.e.*, how rehabilitation staff in the facilities decide which components they will and can replicate); ii) the context (*i.e.*, evaluation of the preparedness of the context to embrace and sustain implementation); and iii) how the change is facilitated (*i.e.*, how and what supports the unit managers use to introduce, implement and sustain the new model) at the study sites.

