#### Quantitative data

##### Patient characteristics

Age, sex, education level, cognitive status (Mini-Mental State Exam; MMSE) [34], pre-fracture cognitive decline (Informant Questionnaire on Cognitive Decline in the Elderly; IQCODE) [35], delirium (Confusion Assessment Method; CAM) [36], delirium severity for those with delirium (Delirium Index) [37], pre-fracture functional status (Older Americans Resources and Services Instrument; OARS) [38], co-morbidities (the number of medical diagnoses), and social support (living alone or with someone). Level of education, level of social support, OARS, and IQCDODE, are being collected from the collateral informant.

In this way, patient’s recall bias will not be a concern. Sex, age, and co-morbidities will be obtained from the National Rehabilitation Services (NRS) database, as these data are collected by all rehabilitation facilities in Ontario. MMSE, CAM and Delirium Index are being collected by the research associate (RA) on admission and at discharge. Every week the RA will also do a CAM to screen for delirium for every patient enrolled in the study because up to 61% of elderly patients post-surgery may become delirious during their stay [7].

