### Data analysis

Objective #1: The primary objective is to determine the impact of PCRM-CI on improvements in mobility (FIM locomotion and mobility) at discharge. At each site and for Usual Care and PCRM-CI groups, mobility is to be assessed at entry into rehab and at discharge from rehab. The change scores for patient outcomes will be compared with paired t-tests by cohort and site. In secondary analyses, multivariate regression will be used to examine the independent effects of each independent variable of interest on patient outcomes while controlling for other predictors and patient baseline factors**.**

Objective #2 (1 & 2): In the second instance, the mobility and physical functioning change scores and return to prior residence for Usual Care patients will be compared to those for PCRM-CI patients to assess the relative impact of the PCRM-CI model on outcomes for each site. Cross tabulations will be employed to assess rates of return to residence by rehab program and site. In particular, patients with CI are to be specifically targeted in the PCRM-CI model. We will compare means of mobility and physical functioning gains scores for patients with and without CI by program and site to assess the relative impact of the PCRM-CI model on patients with CI. In secondary analyses, multivariate regression will be used to examine the independent effects of each independent variable of interest on patient outcomes while controlling for other predictors and patient baseline factors**.**

Objective #2 (3): The introduction of the PCRM-CI model on the two units is meant to a) improve HCPs’ knowledge and attitudes toward working with hip fracture patients with CI, and b) measure the impact on provider satisfaction and work stress of working with these patients.

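### The primary objective is framed on hip fracture patients with cognitive impairment (CI), but the Objective #1 analysis takes whole cohorts whose CI mix was changed between periods; the passages need reconciling.

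*Protocol article*

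**What the plan says.** **The question is put in terms of CI.** The primary objective concerns "an inpatient rehabilitation model of care targeting community dwelling individuals with hip fracture and CI (dementia and/or delirium), results in improved mobility" at discharge. The abstract describes the study as "comparing an inpatient rehabilitation model of care for community dwelling individuals with hip fracture and CI (PCRM-CI) to usual care". The Background gives the overall purpose as to "establish a best practice model that will allow hip fracture patients with CI to regain their mobility and function". Secondary objective 1 opens "To determine whether the PCRM-CI model for persons with hip fracture and CI results in" and lists 6-month mobility, physical function and return to the previous living situation. The Discussion states its hypothesis for clients with CI.

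**The cohorts are not restricted to CI.** The abstract says "All community dwelling (private home or retirement home) patients following a hip fracture are eligible to participate". None of the inclusion or exclusion criteria under Setting and sample concerns CI. Secondary objective 2 needs both kinds of patient, since it looks at mobility at discharge and "6 months post-discharge for patients with and without CI".

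**Nor is the primary analysis.** Under Data analysis, Objective #1: "At each site and for Usual Care and PCRM-CI groups, mobility is to be assessed at entry into rehab and at discharge from rehab". Change scores are then tested by cohort and site. CI status first appears under Objective #2, as a comparison of mean gains with and without CI by program and site.

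**Two further statements matter.** The Background describes a model for all hip fracture patients, with some components aimed at those with CI. The Data collection section says that admission criteria were revised after the usual care period so that more patients with CI could be admitted.

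**The concern.** If the question is the effect in patients with CI, the primary result does not answer it. A positive whole-cohort result could come from patients without CI. A null result could reflect little effect in those patients rather than failure in the target group.

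The change in admission criteria adds a second problem. The Background names CI as one of the most important predictors of poor prognosis for walking ability. If the share of CI patients rises between cohorts, the mean gain can move for that reason alone, and an unadjusted all-patient contrast attributes the movement to the model.

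The definition of CI also needs care. CI includes delirium, the model aims to prevent delirium, and "Every week the RA will also do a CAM to screen for delirium for every patient enrolled in the study". A CI label that used screening after admission could itself be altered by the intervention.

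**Working it through.** **Inputs from the Sample size section:** mean gain 7.2 (usual care) and 12.1 (PCRM-CI), difference 4.9, SD 5.7, two-sided alpha 0.05, power 80%, 70 per cohort.

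**Assumption:** the CI share of the cohorts is not given. I use 31%, 50% and 65%; the ends are the Background's range for older orthopedic patients, who are not the same population as rehabilitation admissions.

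**1. The plan's own figures.** n per group = 2(1.960 + 0.842)² × 5.7² / 4.9² = 21.2, so 22. The exact two-sample t calculation gives 22.24, rounded up to 23. The stated 23 reproduces when read as per group. The stated 39 per group for 80% v 50% return to the community also reproduces. The arithmetic is sound; the question is which patients it applies to. The 80% is a pilot rate in patients with CI, while the 70 per cohort need not have CI.

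**2. Case-mix shift with no model effect.** Assume usual-care gains of 7.2 with CI and 10 without, and a CI share rising from 31% to 65%:
- Usual care cohort: 0.31 × 7.2 + 0.69 × 10 = 9.13
- PCRM-CI cohort: 0.65 × 7.2 + 0.35 × 10 = 8.18
- Shift: 8.18 - 9.13 = -0.95

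With a non-CI gain of 9 the shift is 0.34 × (7.2 - 9) = -0.61; with 12 it is 0.34 × (7.2 - 12) = -1.63. The sign depends on CI patients gaining less under usual care, which is assumed.

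**3. All-patient comparison, 70 v 70, equal CI share s in both cohorts.** Expected difference = 4.9 × [s + k(1 - s)], where k is the fraction of the effect seen in patients without CI. Power is for a two-sample t-test at SD 5.7.

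| CI share | k = 0: difference, power | k = 0.5: difference, power | k = 1: difference, power |
|---|---|---|---|
| 31% | 1.52, 35% | 3.21, 91% | 4.9, 99.9% |
| 50% | 2.45, 71% | 3.68, 97% | 4.9, 99.9% |
| 65% | 3.19, 91% | 4.04, 99% | 4.9, 99.9% |

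**4. CI patients only, difference 4.9.**
- Equal shares: 70 × s gives about 22, 35 or 46 per cohort, with power of 80%, 94% or 98%.
- Unequal numbers, which the change in admission criteria makes more likely: 10 v 35 gives about 65%, and 14 v 35 about 76%. These counts are illustrative.

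**The case against.** The strongest reply is that the texts can be read as consistent. In the primary objective, the word for targeting describes the model and not the analysis set. The Background says the model is for all hip fracture patients, and the pilot covered patients with and without CI. On that reading, open eligibility and a whole-cohort test answer the objective as stated. This reading is possible, and it is why the point is one of reconciliation. It does not remove the conflict: the abstract, overall purpose, secondary objective 1 and Discussion all name CI patients as those meant to benefit, and secondary objective 2 treats patients with and without CI as a separate question.

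A reader might infer that the primary test is necessarily diluted, and that a CI-only analysis would have more power with fewer patients. The documents do not support that. Daily therapy, goal setting, and the pain, falls and sleep sessions are not specific to CI, and delirium prevention can help patients who are not impaired at admission. If patients without CI gain half the effect, all-patient power (91%, 97%, 99%) is above CI-only power (80%, 94%, 98%). Equal CI shares in both cohorts also sit badly with the revised admission criteria.

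A reader might also infer that weekly delirium screening defines CI status. The article does not say so; that is a risk to close, not an error.

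Finally, Objective #2 already compares gains by CI status, program and site, and regression on baseline factors is planned. That covers part of the question, but the first is not the primary test and the second is a secondary analysis. CI cut-offs may properly sit in an analysis plan that is not shown, so their absence is not part of this point.

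**Conclusion.** The concern holds as a mismatch between the stated question and the stated primary analysis. Following the plan gives no primary estimate in patients with CI, and nothing in the primary comparison adjusts for the change in CI mix between cohorts. Neither conclusion depends on the power figures.

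The size is uncertain. The case-mix shift is about -0.95 points against a planned difference of 4.9, and runs from -0.61 to -1.63 over the non-CI gains tried; the gains and shares are all assumed. Dilution runs from severe (35% power at a 31% CI share with no effect in patients without CI) to none (equal effect). The documents give neither the CI share nor the non-CI effect, so dilution should be described as possible. The zero-effect figures are a worst case.

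**What to change.** Before the intervention cohort is analysed, state the target population and match the primary analysis to it.

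**If patients with CI are meant:** fit one model of mobility gain with cohort, admission CI status, cohort × CI and site. Take the cohort effect in patients with CI as primary and the all-patient effect as secondary. Suggested wording: *CI status is defined only from admission MMSE, CAM and IQCODE, with cut-offs fixed in advance; later CAM results do not change it.*

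**If all hip fracture patients are meant:** reword the primary objective to say so, and adjust the primary comparison for admission CI.

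**Cost.** No new data are needed, since the three admission measures are already collected. The CI-specific option has real downsides:
- Fewer patients inform the primary estimate, and 70 per cohort guarantees no minimum number with CI.
- A CI-only test of return to the community (80% v 50%) would have about 55%, 76% or 86% power at CI shares of 31%, 50% or 65%.
- The change comes after the data on all 70 controls were collected, in a study without randomisation, so it should be dated and recorded as such. The article reports 45 of 70 intervention patients enrolled, so it can still precede that cohort's analysis.
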